#### Control Group (Placebo)

Patients with mild AD in the control group will undergo 3 treatment sessions with the placebo (HBL without CAPCS) every day for 4 weeks. The HBL placebo is produced and provided by Shell Party Innovations Technology (Shenzhen) Co, Ltd, which maintains complete consistency in HBL in terms of appearance, weight, color, odor, and package, except for the incorporation of CAPCS (Figure 1). The application, individual guidance, and instruction regarding HBL placebo use in the control group will be completely in line with that in the treatment group. Patients in the control group will also be instructed not to use any additional treatment for AD. Like before, if a patient uses additional treatment for an emergency condition, detailed information will be recorded and the patient will be asked to withdraw from the trial.

**Figure 1 figure1:**
[figure not shown]
Images of HBL used for the 2 study groups. CAPCS: calcium-based antimicrobial peptide compounds; HBL: Haidebao Body Lotion.

#### Follow-Up

In this study, all patients will undergo a physical examination and skin lesion evaluation at baseline (day 0) following enrollment and then will be followed up for 4 weeks subsequently and undergo treatment efficacy evaluation at weeks 2 and 4. Detailed information about data collection, physical examination, and skin lesion evaluation is shown in Table 1.

**Table 1 table1:** Detailed information about the timeline for data collection, physical examination, and skin lesion evaluation.

Study period	Enrollment (day 1)	Baseline (week 0)	Follow-up (week 2)	Follow-up (week 4)
Informed consent	Yes	N/A^a^	N/A	N/A
Screening	Yes	N/A	N/A	N/A
Clinical assessment	Yes	N/A	Yes	Yes
Medical history	Yes	N/A	Yes	Yes
Laboratory examination	Yes	N/A	N/A	Yes
Taking photos of lesions	N/A	Yes	Yes	Yes
NRS^b^ for itching	N/A	Yes	Yes	Yes
EASI^c^	N/A	Yes	Yes	Yes
DLQI^d^	N/A	Yes	Yes	Yes
Drug use	N/A	N/A	Yes	Yes
Adverse effects	N/A	N/A	Yes	Yes

^a^N/A: not applicable.

^b^NRS: Numeric Rating Scale.

^c^EASI: Eczema Area and Severity Index.

^d^DLQI: Dermatology Life Quality Index.

### Outcomes

#### Primary Outcome

In this study, the primary outcome is set as the proportion of patients who achieve EASI_60_ at week 2. The EASI_60_ is defined at least 60% improvement in the EASI score from baseline to week 2, which is calculated as (EASI at baseline – EASI at week t)/(EASI at baseline) × 100%.

#### Secondary Outcomes

##### EASI Score

The EASI score is commonly used to evaluate the condition of AD that is based on the severity of erythema (E), edema/papules/infiltration (I), desquamation (D), and lichenification (L) of the patient’s skin lesions and the affected area of involvement of the skin lesions in the head and neck (H), upper limbs (U), trunk (T), and lower limbs (L). The EASI score is calculated as H(E + I + D + L) × 0.1 + U(E + I + D + L) × 0.2 + T(E + I + D + L) × 0.3 + L(E + I + D + L) × 0.4, in which the affected area of involvement of the skin lesion (H, U, T, L) is evaluated through a 7-point Likert scale, with 0=0%, 1≤10%, 2=10%-29%, 3=30%-49%, 4=50%-69%, 5=70%-89%, and 6=90%-100%. The severity of erythema (E), edema/papules/infiltration (I), desquamation (D), and lichenification (L) is assessed through a 4-point Likert scale, with 0=none, 1=mild, 2=moderate, and 3=severe [27]. The EASI score ranges from 0 to 72, with a higher score suggesting that the patient is more ill. In this study, EASI scores will be assessed at baseline (week 0), week 2, and week 4 after treatment, and EASI50 and EASI75 scores will be assessed at weeks 2 and 4.

##### NRS Score

In this study, we will use the Numeric Rating Scale (NRS, score 0-10) to evaluate the degree of pruritus in patients with mild AD. The NRS is an 11-point Likert scale scored from 0=no pruritus to 10=extreme pruritus. The degree of pruritus will be categorized as no pruritus (NRS=0), mild pruritus (NRS=1-3), moderate pruritus (NRS=4-6), severe pruritus (NRS=7-8), and extremely severe pruritus (NRS=9-10) based on the NRS score [28,29]. In this study, we will assess the degree of pruritus in patients with mild AD before HBL application and at 1, 5, 10, 15, and 30 minutes following HBL application at baseline. We will also assess the degree of pruritus based on the NRS score once at weeks 2 and 4 after treatment.

##### IGA Score

The investigator’s global assessment (IGA) score will be used to estimate the overall condition of patients with mild AD. The IGA is a 6-point Likert scale, with 0=no erythema or inflammatory signs of AD, 1=minimal erythema and barely perceptible edema/papules/infiltration, 2=mild erythema and edema/papules/infiltration, 3=moderate erythema and edema/papules/infiltration, 4=severe erythema and edema/papules/infiltration, and 5=extreme skin lesions accompanied with severe erythema and edema/papules/infiltration [30]. In this study, the IGA score will be estimated at baseline (week 0), week 2, and week 4.

##### DLQI Score

The Dermatology Life Quality Index (DLQI) focuses on various impacts of skin diseases on patients in the last week, which mainly covers 7 dimensions: physiological response, psychological feeling, family, interpersonal communication, occupational restrictions, social activities, and treatment response [31]. The DLQI includes 10 items, all scored through a 4-point rating system of 0=none, 1=mild, 2=severe, and 3=extremely severe (see Table 2). The DLQI score is obtained by summing up the scores of each item, which ranges from 0 to 30, with a higher score suggesting lower dermatology life quality [32]. In this study, the DLQI score will be estimated at baseline (week 0), week 2, and week 4.

**Table 2 table2:** Questions and answer options in the DLQI^a^.

Question number	Question (over the last week)	Options
1	How itchy, sore, painful, or stinging has your skin been?	a. None b. Mild c. Severe d. Extremely severe
2	How embarrassed or self-conscious have you been because of your skin?	a. None b. Mild c. Severe d. Extremely severe
3	How much has skin disease affected your shopping and household chores?	a. None b. Mild c. Severe d. Extremely severe
4	How much has your skin influenced the clothes you wear?	a. None b. Mild c. Severe d. Extremely severe
5	How much has your skin affected any social or leisure activities?	a. None b. Mild c. Severe d. Extremely severe
6	How much has your skin made it difficult for you to play any sport?	a. None b. Mild c. Severe d. Extremely severe
7	How much has your skin condition interfered with your ability to work or study?	a. None b. Mild c. Severe d. Extremely severe
8	How much has your skin created problems with your partner or any of your close friends or relatives?	a. None b. Mild c. Severe d. Extremely severe
9	How much has your skin caused any sexual difficulties?	a. None b. Mild c. Severe d. Extremely severe
10	How difficult is it for you during the treatment process, such as time delays?	a. None b. Mild c. Severe d. Extremely severe

^a^DLQI: Dermatology Life Quality Index.

##### Adverse Events

In this study, patients with mild AD will be informed of the risks that may arise in the study before they sign the informed consent form. We have defined adverse events as unintended signs, symptoms, or diseases occurring after treatment that are not necessarily related to the intervention. The occurrence of any adverse events will be accurately recorded in the case report form (CRF). In this study, appropriate treatment will be provided by dermatologists when they encounter adverse events, and the adherence condition of patients and adverse events will be recorded.

### Withdrawal and Dropout

According to the Declaration of Helsinki, all participants will be respected and can withdraw from the study at any time for any reason. The personal information about participants will be collected and kept confidential. In this study, patients can withdraw at any time, and the reason for withdrawal will be recorded in the CRF.

### Ethical Considerations

This study was reviewed and approved by the Ethics Committee of Shanghai Dermatology Hospital and the Institutional Ethics Review Committee of the Shanghai Skin Diseases Hospital in 2023 (approval number 2023-33). The implementation of the study will strictly adhere to the Declaration of Helsinki. Any adverse events, violations, and amendments to the study protocol or informed consent form will be reported to the Ethics Committee of the Shanghai Skin Diseases Hospital. All patients will sign the informed consent form before enrollment, and participant information will be protected.

### Quality Control

In this study, we will implement a series of measures to improve data quality and ensure the reliability of collected data. First, we will implement a pilot study to train all investigators participating in this study and to evaluate the reliability and validity of the CRF used for data collection. Second, we will assign two PhD students as the inspectors to conduct comprehensive checks in order to ensure the accuracy and integrity of the collected data. Third, we will actively contact all recruited patients during the 4 weeks of follow-up because frequent communication will enhance the patients’ trust and thereby increase their willingness to participate and remain in the study.

### Statistical Analysis

In this study, all data will be recorded in the CRF and then input into a database established using Epidata 3.1 software. The full analysis set (FAS) and the per protocol set (PPS) will be analyzed using the SAS 9.2 statistical package, and missing data will be processed using the multiple imputation method. In this study, quantitative variables with a normal distribution will be expressed as means (SDs), while quantitative variables with a skewed distribution will be expressed as medians (IQRs). Qualitative variables will be expressed as frequency counts and proportions (%). We will apply the 2-sample Student *t* test or the Wilcoxon rank-sum test to examine differences between groups for quantitative variables, as appropriate, and repeated measurement data will be analyzed using repeated-measure ANOVA. The Wilcoxon rank-sum test, the chi-square test, or the Fisher exact test will be performed to examine the differences between groups for qualitative variables, as appropriate. In this study, *P*<.05 (2-tailed) will be considered statistically significant.

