### Sample Size

In this study, the sample size was calculated based on the proportion of patients achieving at least 60% improvement (defined as the effective rate) in the Eczema Area and Severity Index (EASI) score from baseline to week 2 (EASI_60_) in both the treatment group and the control group. A previous pilot study (data not published) indicated that the proportion of EASI_60_ achievement at week 2 was 50% in the CAPCS group and 20% in the placebo group. In addition, a previous open-label clinical trial involving 60 pediatric patients with AD demonstrated comparable efficacy outcomes, with CAPCS combination therapy showing a 42.86% response rate versus 7.14% for the control group at week 2, with statistically significant differences (*P*<.05) [25]. In this study, we used the following formula to calculate the sample size:

We set the proportion of EASI_60_ achievement at week 2 in the treatment group to p1=45%, the proportion of EASI_60_ achievement at week 2 in the control group to p2=20%, the type I error to α=0.05, the type II error to β=0.1. The sample size calculation indicated that at least 70 patients be recruited in each group. Considering a 20% dropout rate and a 10% multicenter effect, we plan to enroll 100 patients with mild AD in each group, for a total of 200 patients with mild AD.

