### Participants

In this study, AD will be confirmed in accordance with Williams diagnostic criteria [26], and patients with AD will be recruited and screened from 10 tertiary hospitals in China from October 2023 to October 2025 by publishing recruitment announcements in newspapers or on information platforms of the hospital official websites, display boards outside the clinics, and information counters. All patients are required to sign informed consent forms before the study begins.

In this study, patients will be included if they meet the inclusion criteria as follows: (1) diagnosis of AD according to Williams diagnostic criteria, (2) age 18-55 years for both males and females, (3) a target lesion with a diameter of 2-10 cm located on the limbs or the trunk, (4) EASI score<6, and (5) skin area<5% body surface area before treatment. The exclusion criteria are as follows: (1) pregnant or lactating women; (2) patients who have undergone AD system treatment within 3 months or local treatment or phototherapy within the past 2 weeks at the time of recruitment; (3) patients with serious systemic diseases or disorders of the heart, lungs, liver, or kidneys or mental illness; (4) patients who are allergic to calcium supplements; (5) patients with systemic disease or an active skin condition (eg, psoriasis) that affects the evaluation; (6) patients with scars, birthmarks, tattoos, freckles, etc; (7) patients with bacterial, viral, or fungal infections requiring anti-infective therapy; (8) patients who have participated or are currently participating in clinical trials of other drugs within the past month; and (9) patients with communication barriers, unable to complete the questionnaire.

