### Limitations

This study may have a few limitations. First, the study period is set to 4 weeks, which limits the observation of the long-term effects of HBL incorporated with CAPCS, as well as its efficacy in prevention of disease recurrence in patients with AD. Second, differences in climate (temperature, humidity, ultraviolet radiation, seasonal changes), lifestyle habits (high-fat food consumption, high-calorie diets, tobacco smoking, alcohol drinking) and other extrinsic factors (cultural differences, occupational exposure, etc) in the 10 selected hospitals may cause information bias, which should be adjusted through sensitivity analysis and subgroup analysis. Third, patients in this study will be instructed not to use any additional treatment for AD, which might induce a relatively high rate of withdrawal in them.

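### The stated tests for week-2 EASI60 use neither baseline EASI nor hospital: valid, but a modest loss of efficiency and out of step with the 10% multicenter allowance

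*Protocol article*

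**What the plan says.** The Primary Outcome section states that "the primary outcome is set as the proportion of patients who achieve EASI"60 at week 2, a yes/no outcome for each patient. The Statistical Analysis section does not name a primary test separately. For qualitative variables it says: "The Wilcoxon rank-sum test, the chi-square test, or the Fisher exact test will be performed to examine the differences between groups for qualitative variables". The choice among them is left open, and significance is judged two-sided. It names no covariate, stratum or model for a binary outcome. It also plans multiple imputation and does not say how results are combined.

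Baseline EASI is collected at week 0 (Table 1 and the EASI Score section). Eligibility caps it ("4) EASI score<6") and states no minimum.

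Hospital appears in two places. The Sample Size section enlarges the trial: "Considering a 20% dropout rate and a 10% multicenter effect". The Limitations section lists differences between the 10 hospitals in climate, lifestyle and other factors, "which should be adjusted through sensitivity analysis and subgroup analysis". The randomization section describes blocks of 4 and 6 and mentions no stratification by hospital.

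**The concern.** Two things do not fit together.

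First, a percentage-reduction endpoint in patients with very low scores can depend on the starting score. That score is in the database, and no stated comparison of EASI60 uses it. A chance imbalance in baseline EASI would stay in the estimate, and whatever precision the covariate offers would be given up.

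Second, part of the sample was added for differences between hospitals, but no stated test takes hospital into account. Of the two remedies in the Limitations section, subgroup analysis describes how the effect varies and does not adjust the overall comparison. Sensitivity analysis could adjust it, but the article does not say what that analysis would be.

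**Working it through.** **1. The plan's own sample size.** Inputs from the Sample Size section: response "in the treatment group to p1=45"% against 20% in the control group; "the type I error to α=0.05, the type II error to β=0.1". Two-sided testing comes from the Statistical Analysis section.

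Pooled formula: n = [z(0.975)·√(2·p̄·(1−p̄)) + z(0.90)·√(p1(1−p1)+p2(1−p2))]² / (p1−p2)², with p̄ = 0.325.

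n = [1.960·√0.43875 + 1.282·√0.4075]² / 0.0625 = 71.7, so 72 per arm. The unpooled version gives 68.5, so 69. The stated 70 lies between them.

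Inflation: 72/0.8 = 90 for dropout, then 90/0.9 = 100 for the multicenter effect. Alternatively, 70/(1−0.3) = 100. On the first route the multicenter allowance accounts for 10 patients per arm. The trial is therefore sized for an unadjusted comparison of two proportions plus a centre margin. Power of that comparison is 89.3% at 70 per arm, 92.9% at 80 and 97.0% at 100.

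**2. Why baseline EASI may matter.** Take a patient with one affected region and area score 1. By the EASI formula, the score is the region weight times an integer severity sum S. Every such patient is eligible on EASI, since the largest possible value is 0.4 × 12 = 4.8. The smallest reduction that counts as a response is:

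| S at baseline | Largest S at week 2 | Reduction needed |
|---|---|---|
| 1 | 0 | 100% |
| 2 | 0 | 100% |
| 3 | 1 | 66.7% |
| 4 | 1 | 75% |
| 5 | 2 | 60% |
| 6 | 2 | 66.7% |

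The effective hurdle thus depends on where the patient starts.

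**3. Size of the effect on power.** The documents give neither a between-hospital variance nor an association of baseline EASI with response. Both are assumed here, on the logit scale (hospital SD; slope per SD of baseline). The simulation used 3000 trials per scenario, 160 evaluable patients, 10 equal hospitals, unstratified blocks of 4 and 6, and marginal response of 45% against 20%.

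| Hospital SD / baseline slope | Chi-square | Mantel-Haenszel by hospital | Logistic with baseline | Change from baseline adjustment |
|---|---|---|---|---|
| 0 / 0 | 93.5% | 91.6% | 93.3% | −0.2 |
| 0.3 / 0.3 | 92.6% | 91.0% | 92.8% | +0.2 |
| 0.5 / 0.5 | 92.4% | 91.6% | 93.5% | +1.1 |
| 0.8 / 0.8 | 93.1% | 93.2% | 94.5% | +1.4 |
| 0 / 0.8 | 92.5% | 91.2% | 94.7% | +2.2 |
| 0.8 / 0 | 92.9% | 93.5% | 92.5% | −0.4 |

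With a stronger assumed slope of 1.0 per SD, the gain from baseline adjustment is about 3 points. With all 200 patients evaluable, chi-square power is 96.9–97.7% and baseline-adjusted power 97.1–98.5%.

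Type I error over both sizes was 4.6–6.0% for chi-square and 4.2–5.4% for the logistic model (Monte Carlo standard error about 0.4 points).

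**4. Hospital as ten fixed effects.** With 160 evaluable patients there are 160/10 = 16 per hospital, 8 per arm. Expected responders per hospital are 8 × 0.45 + 8 × 0.20 = 5.2, and fewer where recruitment is low. In simulations of a logistic model with baseline and ten unpooled hospital terms, between 1% and 28% of trials, depending on scenario, failed to converge or gave extreme coefficients. When neither factor was prognostic, power fell by about 1 to 1.5 points. The Mantel-Haenszel column shows a loss of 1.3 to 1.9 points where the hospital SD is 0.

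**The case against.** **The unadjusted test is legitimate.** No stratification by hospital is described, so no design factor is left out of the analysis. Under 1:1 randomization the simple comparison is unbiased, its type I error stays near 5%, and it matches the sample-size formula. This stands. A reader might infer that the primary result would be biased or invalid; neither the design described nor the simulations support that.

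**The list is generic.** The article says *as appropriate* for all qualitative variables, and a fuller plan might name a model. That is a fair caution. Still, the tests the article does state for a binary outcome are all unadjusted, and a model would change what is published.

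**Hospital is not ignored everywhere.** The Limitations section foresees sensitivity analysis, which could be a hospital-adjusted model, and the 10% can be read as a margin for heterogeneity. This stands too. The gap is only that no stated test corresponds to the allowance.

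**Multiple imputation.** A reader might infer that the stated tests cannot be combined with the planned imputation. The article is silent on combination, which is a detail commonly left to the analysis plan. Chi-square statistics can be combined over imputed data sets, and a risk difference with its standard error pools directly by Rubin's rules. Only a Fisher P value has no natural route. This is not a finding.

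**The EASI table is illustrative.** It covers one region with area score 1, and the baseline distribution is unknown. It shows that the hurdle varies with baseline, but not that the relation is strong or linear.

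**Conclusion.** The point holds as one of efficiency and consistency. The only tests stated for week-2 EASI60 are unadjusted, a plausible prognostic baseline value is already collected, and the 10% multicenter allowance has no counterpart in any stated test. Baseline adjustment is worth about 0 to +3 points of power at 160 evaluable patients, from a starting level near 93%, and costs almost nothing if baseline proves uninformative. These figures rest on assumed logit-scale effects, normally distributed baseline values and response rates of 45% and 20%.

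Adjusting for hospital is less clear-cut. It gains little unless hospitals differ substantially, costs about 1 to 2 points if they do not, and as ten fixed effects risks separation. The planned 200 patients need not change.

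**What to change.** Before unblinding, name one primary analysis: logistic regression of week-2 EASI60 on treatment and continuous baseline EASI. Report the standardized risk difference with 95% CI, combined over imputations by Rubin's rules. Keep the unadjusted chi-square test as supportive.

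Account for hospital in a way that tolerates sparse centres: a random intercept, or small hospitals pooled by a rule set blind to treatment. This can sit in the primary model or in a named sensitivity analysis. Reword the Limitations sentence to point to that analysis, and keep subgroup analysis for describing heterogeneity.

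The cost is analysis-plan wording and a short addition to the SAS program. Baseline EASI is already recorded, hospital follows from the design, and the article reports that data analysis has not yet been performed, so the change can still be prespecified.

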## Results

The flowchart of this study is shown in Figure 2. Participant recruitment began in January 2024 and is proposed to be finished by July 2025. As of May 2025, we enrolled 180 patients, with 160 (88.9%) completing the 2-week follow-up. Data collection and management are still ongoing, and data analysis has not yet been performed.

**Figure 2 figure2:**
[figure not shown]
Study flowchart. CAPCS: calcium-based antimicrobial peptide compounds; DLQI: Dermatology Life Quality Index; EASI: Eczema Area and Severity Index; HBL: Haidebao Body Lotion; IGA: investigator’s global assessment; NRS: Numeric Rating Scale.

## Discussion

### Summary

AD is an autoimmune inflammatory skin disease that can last for a lifetime [33]. AD usually exhibits a chronic course, with thickening of the skin, sleep disturbance, severe life quality interference, and daily activity deprivation, which not only causes physical pain for the patient but also imposes heavy social and economic burdens on them [34,35]. For AD treatment, anti-inflammatory agents, wet-wrap therapy, systemic immunosuppressants, and short-term steroid treatment are used to manage persistent or severe AD cases [11]. However, the use of local and systematic treatment often fails to provide long-term disease control due to safety concerns. As adjuvant therapy, the external application of moisturizing emollients is the basis for AD treatment, which can not only improve the hydration of the cuticle and reduce inflammation [15] but also repair the damaged skin barrier, decrease the stimulation of external factors, and reduce the attack frequency and disease severity [16]. In recent years, the development of new active ingredients has led to the widespread clinical application of emollients to improve the skin barrier in patients with AD.

CAPCS, as new active ingredients, are derived from farmed marine shellfish. Previous studies indicate that the active calcium in CAPCS can inhibit the release of inflammatory mediators and exhibit anti-inflammatory and anti-allergic properties. Moreover, HBL incorporated with CAPCS has similar therapeutic effects as desonide cream in scratch control and itching alleviation in mice and in patients with AD [21], but there is a lack of high-quality clinical trial evidence. This protocol outlines the basic principle and design of a multicenter, double blind, randomized, placebo-controlled trial with 200 patients with mild AD in China. We plan to evaluate the treatment efficacy and safety of HBL incorporated with CAPCS in the enrolled patients, which is expected to yield more generalizable evidence due to the diversity in geography, climate, and participants from the 10 selected hospitals. To the best of our knowledge, this is the first multicenter clinical trial that will recruit 200 patients with AD to evaluate the treatment efficacy and safety of HBL incorporated with CAPCS in China. The clinical data of patients with AD will be extracted from the health information system (HIS) directly without recall bias, resulting in high data quality.

